#### Physiological and biological measures

Serum BDNF is measured in blood samples and assayed using the Human proBDNF and mBDNF DuoSets [83, 84]. We use an ambulatory electrocardiogram (ECG) [85] to measure HRV. Physical fitness is measured by the Ekblom-Bak submaximal cycle ergometer test [86], the Five-Minute Pyramid Test [87] is used for prediction of maximal oxygen uptake (VO_2_ max) and items from the Senior Fitness Test are used for measuring submaximal physical strength [88].

The study will investigate potential mediators and moderators of treatment outcome. Cortisol is measured in three saliva samples collected during the assessment days, and is analysed using the cortisol saliva luminescence immunoassay [89]. Genetic material is obtained by one saliva sample at baseline, and analysed using the TaqMan method [90]. Participants wear the Philips Actiwatch 2 [91] for 1 week at baseline, post-intervention and at 12-month follow up to measure activity level and sleep variables.

A subsample of 40 participants undergo MRI at baseline, post testing and at 12-month follow-up testing. MRI will be performed using a GE Signa 3 .0T twin speed HDxt scanner [92]. A head coil with video goggles allows for the Eriksen flanker task [93] to be applied during functional MRI.

### Procedures

This study will be conducted at an outpatient clinic at Solli DPS, a local mental health facility. The neuropsychological testing and MRI will take place at Haukeland University Hospital, in cooperation with the University of Bergen. There are five test points for each participant: baseline, interim, post-treatment and 6-month and 12-month follow up. We have designed the pattern of test points for the investigation both of treatment mechanisms and treatment outcome.

#### Baseline testing

The baseline testing consists of several elements: (1) a start-up conversation with a project coordinator, whereby the participant completes questionnaires, receives saliva samplers with instructions and receives an actigraph watch; (2) a physical/physiological test day, when the participants undergo ECG, provide a saliva sample for DNA testing and blood samples for measurement of BDNF and undergo tests of physical fitness and strength; (3) an appointment for neuropsychological testing and (4) an appointment for functional magnetic resonance imaging (fMRI).

#### Randomisation

Randomisation is performed anonymously at the University of Bergen in blocks of ten following baseline testing. Randomisation is computerised and concealed [94]. The person conducting the randomisation is blind to participants’ identities and does not have any information on the participants. Blocks of ten were preferred, to achieve predictability for the hospital and staff. This does, however, mean that for every block, the tenth allocation can be determined with certainty if that of the former nine is tracked. Calculations using hypergeometric distributions also show that there is a 4.76%, 16.66% and 44.44% probability that the precise allocation of participants can be known with certainty following 6, 7 and 8 draws respectively. However, information about allocation is not tracked, and was deemed an acceptable risk to achieve practical feasibility of running the trial within a clinical setting.

#### Blinding

This study is single-blinded. We do not disclose to the participants which of the adjunct interventions we expect to be the active intervention. Patients are informed that we investigate two adjunct strategies, and that we will evaluate which of these provides better treatment efficacy. We take great care to inform all involved personnel to convey this message.

The independent clinical assessor, who evaluates remission after treatment, does not know which adjunct intervention the participant received during treatment. The appointment with the independent clinical assessor is scheduled without giving the assessor access to the patient’s medical journal. Also, the project coordinator meets with each patient before the appointment and give instructions not to reveal treatment allocation. After the interview, we ask the independent clinical assessor whether the patient revealed treatment allocation, and make a record of the response.

#### Pre-treatment period

After randomization, the included participants go on to the pre-treatment period with either five weekly sessions of physical exercise or telephone call attention placebo. The pre-treatment period lasts 5 weeks, but can be extended by 2 weeks due e.g. to illness or holidays. If after the maximum extension period the patient has completed fewer than five sessions, the patient proceeds to interim testing. Compliance will be registered for each participant.

#### Interim testing

The interim testing consists of two appointments; a physical/physiological test day, in which participants undergo ECG, provide blood samples for measurement of BDNF, test physical fitness and strength, and are provided with take-home saliva samplers; and an appointment with a project coordinator, whereby the participant completes questionnaires and returns the saliva samplers.

#### Treatment

After interim testing, participants have a start-up conversation with their CBT therapist, followed by 10 weekly sessions of CBT combined with either physical exercise or telephone call attention placebo. The treatment period lasts approximately 11 weeks, but can be extended by 4 weeks due e.g. to illness or holidays. Interventions are scheduled on separate days of the week, so that the participant does not attend both CBT and supervised physical exercise on the same day. We register compliance for each participant.

#### Post-treatment testing

Post-treatment testing starts as soon as possible after completion of treatment, and no later than 2 weeks after the last treatment session. The post-treatment testing corresponds to the baseline testing, with the exception of the DNA saliva sample, which is only provided at baseline.

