**Methods:**

The sample comprises 70 participants aged 60–75 years, who have GAD. Exclusion criteria comprise substance abuse and unstable medication; inability to participate in physical exercise; and conditions which precludes GAD as primary diagnosis. The interventions are individual treatment in the outpatient clinic at the local psychiatric hospital, with two experimental arms: (1) CBT + physical exercise and (2) CBT + telephone calls. The primary outcome measure is symptom reduction on the Penn State Worry Questionnaire. Other measures include questionnaires, clinical interviews, physiological, biological and neuropsychological tests. A subset of 40 participants will undergo magnetic resonance imaging (MRI). After inclusion, participants undergo baseline testing, and are subsequently randomized to a treatment condition. Participants attend five sessions of the add-on treatment in the pre-treatment phase, and move on to interim testing. After interim testing, participants attend 10 sessions of CBT in parallel with continued add-on treatment. Participants are tested post-intervention within 2 weeks of completing treatment, with follow-up testing 6 and 12 months later.

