## Method

### Study design

The study is a 2 × 2 mixed factorial design (Time x Group) with participants randomized to one of two treatment conditions: (1) CBT combined with physical exercise (CBT + PE) or (2) CBT combined with telephone call attention placebo (CBT + AP). Participants complete pre-treatment, interim and post-treatment outcome measures, in addition to follow-up tests at 6 and 12 months after treatment.

Participants in both treatment conditions attend a 5-week pre-treatment period. The pre-treatment period has a two-part rationale. The first 5 weeks of physical exercise are aimed at introducing the participant to the exercises with a focus on adjustment and neuromuscular facilitation [64]. In addition, resting BDNF has been shown to increase after 5 weeks of physical exercise [65]. The primary goal of the pre-treatment period is to ensure good implementation of physical exercise, and to obtain elevated resting BDNF in the CBT + PE group before the onset of CBT. As such, the pre-treatment period is a measure to facilitate the add-on effects of physical exercise.

Participants receiving CBT + PE attend one supervised and two unsupervised sessions of PE during each of the 5 weeks of the pre-treatment period. Participants receiving CBT + AP receive one telephone call per week during the pre-treatment period.

After the pre-treatment period, the participants receive 10 weekly sessions of CBT combined with either continued physical exercise in the participants receiving CBT + PE or weekly telephone contact in parallel to the CBT sessions in the participants receiving CBT + AP. See Fig. 1 for a display of the study design. The present protocol has been prepared in accordance with relevant items from the Standard Protocol Items: Recommentations for Interventional Trials (SPIRIT) Checklist (see Additional file 1). See Fig. 2 for the SPIRIT figure displaying the schedule of enrolment, interventions and assessments.

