### Power analysis and statistical analysis

Power estimates were calculated using the G* Power 3 programme [103]. Treatment effects will be investigated by an intention-to-treat approach to data analysis using a hierarchical linear model, whereby therapists will be included at the second level to account for potential nesting by this factor. Power analysis for effects are estimated with conservative repeated measures analysis of variance (ANOVA) (within-between interactions). For the primary outcome measure, based on previous studies [22, 28], the difference in effect size is set to *d* = 0.35, alpha = 0.05, correlation between repeated measures 0.5, two measurements (pre/post), a total of 70 subjects (*n* = 35 in each group) yielding power above 0.82. Moderators and mediators will be investigated using linear multiple regression, fixed model, single coefficients. An effect size set to *f*^*2*^ = 0.15, two-tailed tests, alpha = 0.05 and *N* = 70 yields power above 0.95 with four predictors. For the subset of functional MRI (fMRI) assessments the following statistics and power analysis will be applied: task-fMRI data will be analysed using General Linear Model in SPM12 for pre-processing and single subject and group analyses, GIFT [104] to investigate the functional and structural data, and arterial spin labelling (ASL) data will be analysed in SPM12. Region of interest (ROI) will be analysed for both structural and functional data (SPM12) to extract blood oxygen level dependent (BOLD) responses to test correlation with specified variables. Expecting percent signal changes of approximately 0.5% at the single voxel and spatial smoothing at full width at half maximum (FWHM) of 5 mm (provides an estimated effect size of *d* = 0,7), using the two-tailed independent samples *t* test, an allocation rate of 1, alpha set to 0.05, correlation between repeated measures 0.5 and a total sample size of 80 (40 in each group) yields power above 0.87. For differences between pre-treatment and post treatment data using the same parameters, the matched-pairs *t* test with 20 subjects yields power above 0.90. Treatment effects are estimated using conservative repeated measures ANOVA (within-between interaction), and conservatively setting the estimated value of *d* = 0.35, alpha set to 0.05, two measurements (pre, post), correlation between repeated measures 0.5, and 60 subjects (*n* = 20 per group) yields power above 0.83. Based on these calculations, the estimated power values indicate that risk of committing type II errors is adequately controlled.

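### The post-treatment PSWQ is timed from each participant's last treatment session, so early stoppers are tested far too soon or not at all, which does not fit the intention-to-treat comparison

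*Protocol article*

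**What the plan says.** All references are to the Protocol article.

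- **Post-treatment visit.** Under Post-treatment testing, the visit is to begin promptly once treatment is complete, and "no later than 2 weeks after the last treatment session". The abstract gives the same anchor and places the later visits after it: "Participants are tested post-intervention within 2 weeks of completing treatment, with follow-up testing 6 and 12 months later". Study design counts them from treatment: "in addition to follow-up tests at 6 and 12 months after treatment". None of these visits is tied to randomisation.
- **Length of the phases.** Under Pre-treatment period: "The pre-treatment period lasts 5 weeks, but can be extended by 2 weeks due e.g. to illness or holidays". Under Treatment: "The treatment period lasts approximately 11 weeks, but can be extended by 4 weeks due e.g. to illness or holidays". The section on cognitive behaviour therapy caps therapy at 15 weeks and allows more than one session in a week, so a course can also be shortened.
- **Incomplete attendance.** For the interim test there is an explicit rule: "If after the maximum extension period the patient has completed fewer than five sessions, the patient proceeds to interim testing". The post-treatment test has no counterpart. Ethical considerations says only that participants in whom an excluding condition is disclosed or develops are discontinued from the trial.
- **Analysis.** Under Power analysis and statistical analysis: "Treatment effects will be investigated by an intention-to-treat approach to data analysis", using a hierarchical linear model. The power calculation uses two measurements, before and after treatment.

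**The concern.** The time-by-group comparison treats the post-treatment PSWQ as one time point. The rule makes its date depend on something that happens after randomisation, namely when treatment ends for that person. For someone who attends the whole course this gives a bounded spread. For someone who stops early it gives either a very early measurement, taken after little or no CBT, or none.

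An intention-to-treat comparison needs the outcome of every randomised participant at a comparable time, whatever treatment was taken. A hierarchical model can handle missing values under assumptions. It cannot make a score from week 6 equivalent to one from week 17 if both are coded as the same occasion. If early stopping is more frequent in one arm, the difference in elapsed time becomes part of the estimated treatment effect.

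**Working it through.** **1. The plan's own figure.** For the primary outcome the article states power above 0.82 with d = 0.35, N = 70, two measurements, correlation 0.5 and alpha 0.05. In the repeated-measures interaction convention, f = 0.35/2 = 0.175 and λ = N·f²·m/(1 − ρ) = 70 × 0.175² × 2/0.5 = 8.575, with 1 and 68 degrees of freedom. This gives power 0.823, so the figure reproduces. It does not depend on visit timing.

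**2. Timing for completers**, in weeks from randomisation, not counting interim-testing time. Week of test = pre-treatment period + treatment period + test window.

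- On schedule: 5 + 11 + (0 to 2) = weeks 16 to 18.
- Fully extended: (5 + 2) + (11 + 4) + (0 to 2) = weeks 22 to 24.
- Spread: 24 − 16 = 8 weeks. Doubling up CBT sessions could bring the lower end forward somewhat.

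Taking 6 and 12 months as 26 and 52 weeks from the post-treatment test, follow-up falls at weeks 42 to 44 and 68 to 70 on schedule, and at weeks 48 to 50 and 74 to 76 when fully extended.

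**3. Timing for an early stopper, literal reading.** Week of test = week of last session + (0 to 2).

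- Last session in week 5: weeks 5 to 7, with follow-up at weeks 31 to 33 and 57 to 59.
- Last session in week 10: weeks 10 to 12.
- Stopping in week 5 therefore puts the test 16 − 5 = 11 weeks before an on-schedule participant, and up to 24 − 5 = 19 weeks before a fully extended one.

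On the other reading, which requires completion, no test is set.

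**4. How much extension could differ by arm.** Of the 2 + 4 = 6 extension weeks, 4 belong to the phase in which both arms attend the same 10 CBT sessions under the same cap. The 2 pre-treatment weeks are the clearly arm-specific part. If the arms differed only there, the mean gap would be 2 weeks × the difference in the proportion using the full extension. A 1-week gap needs a 50-percentage-point difference. A 2-week gap needs everyone in one arm and no one in the other.

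**5. Illustration on assumptions that are not in the documents.** Suppose PSWQ falls by 0.5 to 1.0 SD, linearly over 16 weeks. The slope is 0.5/16 = 0.031 to 1.0/16 = 0.0625 SD per week.

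- Mean gap of 1 week between arms: 0.03 to 0.06 SD.
- Mean gap of 2 weeks: 0.06 to 0.13 SD.
- Early stopping 10 percentage points more frequent in one arm, tested 11 weeks sooner: 0.10 × 11 = 1.1 weeks, or 0.03 to 0.07 SD.

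Against the planned 0.35, the last line is about 10 to 20%. It also assumes that early stoppers would have kept improving at the same rate after stopping, which may be untrue.

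**The case against.** A reader might infer that the arms will be measured at different times and that the primary contrast is therefore biased. The exercise arm has a weekly clinic session and two individual sessions, while the other arm has one short call. Illness or a holiday could interrupt the first without interrupting the second. The documents do not support that conclusion. The extension limits are the same in both arms, most of the extension lies in the shared CBT phase, and no difference in its use is reported. Extension weeks also exist because sessions were interrupted, so a steady decline in worry through them is doubtful.

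A reader might also want every outcome visit moved to one late date from randomisation. That is a trade-off. A common visit at weeks 22 to 24 would test on-schedule participants 6 to 8 weeks after CBT and exercise had ended, which blurs the end-of-treatment BDNF, HRV and fitness measures that the mechanism hypotheses rely on. It would also mix two definitions of the visit, since recruitment opened in September 2017.

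On early stoppers, the other side can say that the last treatment session naturally means the end of the course, and that a post-treatment test before CBT sits badly with the stated order of five test points. It can add that an article often leaves withdrawal visits to the full protocol. This has force against the most extreme examples. Missed pre-treatment sessions alone do not bring a visit forward, because the participant proceeds to interim testing. It does not remove the point. The article fixes the anchor itself, and under either reading someone who leaves treatment has no comparable post-treatment measurement.

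**Conclusion.** The point holds in a limited form. The anchor is stated, and the range of weeks 16 to 24 for completers follows by addition. That range is a defensible consequence of measuring at the end of treatment. What needs changing is the rule as it falls on early stoppers: a test that may come 11 to 19 weeks before other participants' (last session in week 5), or no test, conflicts with the intention-to-treat comparison.

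The size of any bias is unknown. The documents give neither a rate of early stopping nor a rate of worry decline, and they show no imbalance between arms. The illustrative shifts of 0.03 to 0.07 SD rest wholly on the assumptions listed in the check. No stated sample size, power or alpha is wrong on this account.

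**What to change.** Keep the end-of-treatment anchor for participants who complete the course. Amend Post-treatment testing so that every randomised participant who stops treatment early is invited to the post-treatment test at the nominal time from randomisation, about weeks 16 to 18 plus interim-testing time. Count that participant's 6- and 12-month tests from that date. Say whether this covers participants discontinued under Ethical considerations, so that the two sections agree.

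Record weeks since randomisation at each PSWQ, and run a sensitivity analysis of the hierarchical linear model with actual time in place of the nominal occasion. Elapsed time is itself affected by what happens after randomisation, so this should support the primary analysis and not replace it. It also covers visits already made.

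The cost is the effort of inviting early stoppers to later visits, plus one extra analysis. Treatment does not change, and completers' visits stay as they are.

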#### Follow-up testing at 6 months

The 6-month testing corresponds to the interim testing.

#### Follow-up testing at 12 months

The 12-month testing corresponds to the post-treatment testing.

### Interventions

#### Cognitive behaviour therapy (CBT)

Participants attend 10 sessions of individual CBT applied following a manual, in accordance with the protocol developed by Borkovec [17]. One initial session focuses on developing a therapeutic alliance and introducing the therapy before the CBT is applied. The duration of the CBT is approximately 10 weeks. The therapist and participant can agree to increase the number of weeks within reasonable limits, or do more than one session within one week, in case a participant misses one or more CBT sessions (e.g. because of holidays, illness, etc.). If the duration of the therapy exceeds 15 weeks, the participant will not receive the remaining sessions. The project coordinators keep a record of the number of CBT sessions each participant attends. We have adapted the CBT manual to the study in collaboration with [name] from the Norwegian University of Science and Technology. [name] also provides training and supervision to the therapists who perform CBT, who are psychologists or psychiatrists with formal training in CBT and specific education in the study CBT manual. Before treating participants in the PEXACOG study, therapists are required to have performed one full video-documented therapy that has been rated by an external assessor and scored on the Cognitive Therapy Adherence and Competence Scale (CTACS) [95] with a mean score of 3 or higher. Two qualified assessors will evaluate at least 20% of the individual therapists’ treatment courses according to the following procedure: Therapists record all CBT sessions. The recorded sessions will be drawn randomly, stratified by first or second half of the treatment course (i.e. session 1–5 or 6–10). Both assessors will rate each selected recording on the covered domains in the CTACS, and CTACS ratings are compared to determine inter-rater reliability.

The CBT consists of several elements. Participants receive psychoeducation about anxiety and the treatment model. They also learn diaphragmatic breathing, and two versions of a progressive muscle relaxation exercise - one longer version with 7 muscle groups, and one shorter version with 4 muscle groups. These elements receive attention throughout the treatment. Participants complete homework assignments between sessions, including daily registration of anxiety level. Participants receive an mp3 player with recorded instructions on diaphragmatic breathing and progressive muscle relaxation to use between sessions. Furthermore, participants learn cognitive monitoring and restructuring. A key element of the CBT is self-controlled desensitisation. Self-controlled desensitisation is a process whereby participants establish an anxiety hierarchy, learn new responses to anxiety cues, and connect the anxiety cues with the new response. To practice self-controlled desensitisation, participants are asked to worry on purpose, and respond with relaxation when the anxiety levels are elevated. The final treatment session focuses on relapse prevention.

#### Physical exercise (PE)

The duration of the PE programme is 15 weeks. The first 5 weeks comprise the pre-treatment intervention. During the following 10 weeks the participants attend to both PE and CBT. Each week consist of one supervised training session at the local mental health facility (clinic), and two individual training sessions. Supervised sessions are led by physiotherapists or occupational therapist who are trained in the study manual and receive supervision on test procedures and the exercise manual. For the individual training sessions, each participant is given their own exercise journal with instructions, and is instructed to log each individual training session. All participants use a heart rate monitor watch [96], which is used during individual endurance training sessions and monitored by the PE therapist at the supervised training session. This is a measure of patient adherence to the PE. Physical tests at the interim and post testing time points also serve as manipulation checks. The participants complete the GAD-7 questionnaire at each of the supervised training sessions.

The PE programme is adjustable according to the participants’ prerequisites, without compromising the exercise intensity. Each session lasts approximately 45–60 min, and contains both strength and endurance training. The strength training programme consists of seven exercises; squats, push-ups, lunges, rowing with elastic bands, calf raises, dips and shrugs with elastic bands. Endurance training is designed based on interval principles. The exercise intensity progresses every fifth week. The intensity level at the beginning of the intervention period (week 1–5) will be low to moderate (65–85% of maximum heart rate (HR max)). It increases to moderate intensity at week 6–10 (65–90% of HRmax) and at week 11–15 it increases to moderate to high intensity (65–95% of HRmax). This equals 60–70%, 70–80% and 80–90% of one repetition maximum (1RM) [97] when transferred to resistance load in strength exercises [98]. The exercise programme is designed to ensure that participants take part in at least the minimal therapeutic dose of exercise, which is 150 min of moderate intensity activity per week [99, 100].

